#### Control group. Waiting list (WL) control group

The control group will receive no intervention for the first three months after enrolling in the study and complete the first assessment (pre-assessment). After completing the second assessment (3 months), participants in this condition will be informed that they will have access to the iABCT program.

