### Sample size

The sample will be composed of 68 participants as minimum. The sample size was calculated using the G*Power 3.1.9.7 for Windows program [68]. Estimated sample size was decided based on medium effect sizes (d = 0.4), statistical power of .80 and α = .05, indicating a necessary sample of 52 participants [69]. Considering that the dropout rate in Internet-based interventions for the chronic medical ill population is usually around 30%, a target of 34 people per group was set [70–72].

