### Allocation and blinding

After giving online written informed consent to participate in the study and completing online eligibility and baseline questionnaires, participants who meet the criteria will be randomized to the experimental or the WL control group. An allocation scheme will be created by a member of the research team blind to the study using a computerized random generator (random allocation software 2.0) at a 1:1 ratio. Randomization will be stratified by type of chronic medical condition (diabetes, fibromyalgia, intestinal inflammatory illness, migraines, low-back chronic pain and other conditions). After randomization is completed, both researcher and participant will be informed with the results. Participants in the intervention groups will have access to the program right after receiving the outcome, meanwhile participants in the WL control group will have to wait 3 months to have access to the intervention. As both participants and researcher will be informed about which of the two conditions participants are assigned, blinding for the treatment is not possible.

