### Statistical methods

The latest version of SPSS (v.26) will be used for all data analysis. T-tests for independent-samples (t), ANOVAs, and chi-square analysis (χ2) will be calculated to investigate the characteristics of the randomized sampled and included in the RCT and to explore group differences in participants’ sociodemographic (e.g., age, gender) and clinical data (e.g., quality of life, well-being). Attrition and dropout rates will be calculated by reporting percentages and patterns of missing data. Intent-to-treat mixed-model analyses without any ad hoc imputations will be used to handle missing data in case of participant dropout and to conduct the efficacy analysis [73]. This analysis compares the study groups based on the treatment to which they were randomly allocated. It does not assume that the last measurement is stable, it does not involve any substitution of missing values with supposed or estimated values, it is conducted using all available observations, thus reducing the biases and loss of power caused by the simple deletion or random imputation of incomplete data. Mixed-model analyses are appropriate for RCTs with multiple time points and pre-post designs, and it has showed remarkable robustness to violations of distributional assumptions (e.g., skewed, kurtosis, or heteroscedastic) [74, 75]. To study distributional assumptions and the impact of missing random effect components on model some test will be included: Normality assumptions will be explored using the Shapiro-Wilk test (for each experimental group, N < 50), the Kolmogorov-Smirnov (K-S) test (for the total sample, N > 50), skewness and kurtosis indices, and normality plots (Q-Q plots). Homoscedasticity will be explored by Levene’s test and Box’s M test for equivalence of covariance matrices. Wald statistic (or Z-test) will be conducted to test the residual error variance estimation and the null hypothesis of homogeneity of residuals. The assumption that data is missing completely at random (MCAR) will be evaluated using Little’s MCAR test. it is robust to violations of distributional assumptions. A linear mixed-effect model for each outcome measure will be implemented using the MIXED procedure with one random intercept per subject. An identity covariance structure will be specified to model the covariance structure of the intercept. For each outcome, time (baseline and 3- and 6-month follow-up) will be treated as a within-group factor and group (experimental and control group) as a between-group factor and significance effects will be followed up with pairwise comparisons (adjusted by Bonferroni correction). Cohen’s d effect size and 95% CI will be calculated for within- and between-group comparisons [76, 77]. Sensitivity analyses will be performed to assess the robustness of the findings in terms of different methods for handling missing data (i.e., mixed models with and without imputation, maximum-likelihood estimation, and maximum-likelihood multiple imputation [78]. The means and standard deviations of the acceptability measures of the intervention will be analyzed. For analyses of associations between intervention outcomes, predictors of change and mechanisms of action, several statistical tests such as Pearson’s correlation, multiple regressions and mediation analysis will be performed. In addition, participants’ qualitative responses regarding facilitators and barriers to the intervention will be explored using a qualitative content analysis and coding and categorization approach to the data using word frequency counts with ATLAS.ti software.

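### The listed missing-data sensitivity analyses, as normally run, share the primary model's missing-at-random assumption, so their agreement would not show robustness to outcome-related dropout

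*Protocol article*

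**What the plan says.** The protocol article (Statistical methods) makes a likelihood-based mixed model on all available observations both the efficacy analysis and the way of handling dropout. Robustness to the handling of missing data is to be judged from a list introduced by i.e.: "mixed models with and without imputation, maximum-likelihood estimation, and maximum-likelihood multiple imputation". On the mechanism of missingness it says "The assumption that data is missing completely at random (MCAR) will be evaluated", by Little's test. No delta-adjusted, tipping-point, reference-based, pattern-mixture or selection-model analysis is named. The section closes by promising a review of current methods before the data are analysed.

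Three other places bear on this:

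- **Sample size** puts dropout in such trials at "usually around 30%, a target of 34 people per group was set".
- **Control group. Waiting list (WL) control group** links access to the assessment: "After completing the second assessment (3 months), participants in this condition will be informed that they will have access to the iABCT program". Research design says the same.
- **Allocation and blinding** gives the iABCT arm the programme straight after randomisation and states that "blinding for the treatment is not possible".

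**The concern.** A sensitivity analysis for missing data is useful when it varies the assumption that the data cannot test. Here that assumption is missing at random: given what was observed, leavers would have scored like comparable people in their own arm who stayed. A mixed model, maximum likelihood and standard multiple imputation are different ways of computing an answer under it. Little's test sets missing completely at random against weaker mechanisms. The mixed model does not need that condition, and the test cannot see dropout driven by unobserved scores.

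The design gives reasons to doubt missing at random:

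- Assessments fall only at baseline, 3 and 6 months, so someone lost before month 3 contributes baseline data alone. The model then borrows the 3-month course of arm-mates who stayed.
- Waiting-list participants have a reason to complete month 3. iABCT participants already have the programme.
- Assessments sit on the platform that hosts iABCT, so leaving the programme may well mean leaving the assessments.
- The primary outcomes are self-reported and participants know their arm.

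At stake is whether a 3-month effect could be reported as robust when the check had no means of finding it otherwise.

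**Working it through.** **Inputs from the protocol (Sample size).** d = 0.4, a required sample of 52, about 30% dropout, 34 per group.

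**The plan's own dropout figure.** 52 × 1.30 = 67.6, rounded up to 68, which is 34 per group. So 30% is the rate the plan builds in, and 68 × 0.70 = 47.6, about 48 people with follow-up data. (Dividing instead, 52 / 0.70 = 74.3, would give 75. That is a separate matter.)

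**Step 1: size of a departure from missing at random.** Let p_I and p_C be the dropout proportions in the iABCT and waiting-list arms. Let s_I and s_C be the amounts, in SD, by which leavers fall below what missing at random predicts for them. Then

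effect in all randomised = missing-at-random estimate − (p_I × s_I − p_C × s_C).

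The shifts are assumptions; the protocol gives none. Starting from an estimate of 0.40:

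| p_I | s_I | p_C | s_C | Effect in all randomised |
|---|---|---|---|---|
| 0.30 | 0.2 | 0.30 | 0 | 0.40 − 0.06 = 0.34 |
| 0.30 | 0.4 | 0.30 | 0 | 0.40 − 0.12 = 0.28 |
| 0.30 | 0.8 | 0.30 | 0 | 0.40 − 0.24 = 0.16 |
| 0.30 | 1.33 | 0.30 | 0 | 0.40 − 0.40 = 0 |
| 0.40 | 0.4 | 0.20 | 0.4 | 0.40 − 0.08 = 0.32 |
| 0.30 | 0.4 | 0.30 | 0.4 | 0.40 − 0 = 0.40 |
| 0.30 | 0 | 0.30 | 0.4 | 0.40 + 0.12 = 0.52 |

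The second row is the case where iABCT leavers get none of the benefit; it equals 0.70 × 0.4 + 0.30 × 0 = 0.28. The last two rows show that the bias can vanish or reverse. The 40% and 20% rates are assumed.

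**Step 2: would the listed methods reveal it?** Large-sample simulation, N = 400,000, true effect 0.40, 30% dropout in each arm, baseline–outcome correlation 0.5. Dropout is random in the waiting-list arm. In the iABCT arm the log-odds of dropout rise as the unseen 3-month score falls, by the slope shown per SD. All of these settings are assumptions except the 0.4 and the 30%. Maximum likelihood is represented by regression of the outcome on baseline and arm in those observed. Imputation is within arm from baseline.

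| Slope | Maximum likelihood | Imputation under missing at random |
|---|---|---|
| 0 | 0.40 | 0.40 |
| 0.5 | 0.51 | 0.51 |
| 1 | 0.59 | 0.59 |
| 2 | 0.68 | 0.70 |

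The two methods stay within about 0.01 SD of each other (0.684 and 0.695 before rounding in the last row), while both are off by 0.11 to 0.30 SD at the non-zero slopes.

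**Step 3: a case where the listed methods do differ.** Same N, true effect and dropout rate, but iABCT dropout depends on a baseline variable correlated 0.3 or 0.5 with the outcome (slopes 0.5 to 2). Ignoring that variable gave estimates of about 0.44 to 0.60. Imputing with it gave 0.39 to 0.41. So imputation with auxiliary variables can expose dropout related to baseline characteristics. It does not address the mechanism in Step 2.

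**The case against.** Several objections have force.

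- **The imputation model is unspecified.** A reader might infer that every listed method must assume missing at random and must give the same answer. The text does not go that far. A non-standard imputation is not formally excluded, and with auxiliary variables imputation can differ from the mixed model, as Step 3 shows. The trial collects many candidate variables at baseline. Still, nothing in the text points to an imputation outside missing at random or says that auxiliaries will be used.
- **This is a condensed article, and methods will be reviewed before analysis.** Imputation details can fairly be left to an analysis plan. But the article itself states what the robustness check consists of, and a general promise to review methods commits to no analysis that varies the assumption. Nothing in it bars adding one.
- **Little's test is only one of several assumption checks.** A reader might infer that its result decides whether the primary model is valid. No section says so. What stands is that it cannot speak to the mechanism at issue.
- **The dropout story is conjecture.** iABCT participants might leave because they improved, and waiting-list participants because they worsened. Participant timeline and Allocation and blinding also describe waiting-list access by elapsed time, without the condition of a completed assessment. So the direction is unknown. A reader might infer that the reported effect will be inflated by some definite amount, such as 43% (0.40 / 0.28 = 1.43). That follows only from a chosen one-sided scenario and is not a forecast.
- **Part of the reporting is already planned.** Attrition percentages, missing-data patterns and reasons for dropout are to be collected or reported. Only the split by arm is not stated.

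**Conclusion.** The concern holds in a limited form. As normally run, the listed analyses rest on the primary model's own assumption, and Little's test cannot detect a failure of it. With about 30% dropout expected and different incentives by arm to complete month 3, agreement among them would not show robustness to outcome-related dropout. In the illustration, 30% dropout with no benefit among iABCT leavers turns 0.40 SD into 0.28 SD, and a shift of 1.33 SD in those leavers alone would remove the effect. These figures rest on assumed shifts confined to one arm. With equal dropout and equal shifts the bias is zero, and with worse-than-predicted waiting-list leavers it runs the other way. The documents do not support a claim that the estimate will be biased upwards. They support the narrower statement that the planned check could not tell.

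**What to change.** Keep the listed analyses as the missing-at-random anchor and state which variables enter the imputation model. Add one pre-specified missing-not-at-random analysis of the 3-month EQ-5D and PHI contrasts, chosen before the data are seen, from:

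- a delta-adjusted or tipping-point analysis, with shifts varied separately in each arm, reporting the combinations at which the conclusion changes; or
- reference-based multiple imputation, with iABCT leavers imputed from the waiting-list distribution at 3 months, when that arm has not yet received iABCT.

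Report dropout and its timing by arm. Little's test may stay as a description, with a sentence that it does not assess missing at random.

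The cost is a little extra programming and reporting, with no new data, visits or participants. The result may look less favourable.

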### Data management

Online data collected from LimeSurvey and Psychology and Technology platforms will be stored at protected servers of the University of Valencia. Only individuals authorized by the principal investigator will have access to the database. After completing the assessment points, authorized individuals will download the database in a SPSS format that will be automatically saved onto a password-protected cloud server of the University of Valencia (nÚVol, https://nuvol.uv.es).

Database will be stored at online secured servers from the University of Valencia for up to 5 years after the project ends.

### Data monitoring

The research team will be monitoring the proper conduction of the trial and participant safety. During the RCT, participant’s interest will be overseen and safeguarded, the overall conduct of the trial will be monitored, and participants’ safety will be ensured by systematically checking negative events and reacting to any extreme distress. Additional help and counseling will be strongly recommended to participants in the case of any adverse event or emergency.

Periodical meetings will be conducted by the research team after the three assessment points (pre-assessment and follow-up) to ensure the proper progress of the study and the current state of the data collection.

Important protocol modifications will be communicated to relevant parties (i.e., trial participants, trial registries, ethical committee, and researchers).

### Harms

So far, no studies have reported harms with CBIs. In case participants identify signs of mental or physical health detriment during participation, they will be provided with a list of health resources available and strongly recommended to visit their usual health professional.

### Auditing

No audit has been planned at this time.

### Research ethics approval, protocol amendments and consent

This trial will be conducted in compliance with the study protocol, the Declaration of Helsinki, and good clinical practice. Ethical approval for this trial has been obtained for the Ethics Committee of Research in Humans of the Ethics Commission in Experimental Research of University of Valencia (UV-INV_ETICA-1564960) on March 5, 2021.

The study was registered under Clinicaltrials.gov (NCT04809610) and will be conducted following the Standard Protocol Items: Recommendations for Interventional Trials (SPIRIT) guidelines [79]. The SPIRIT checklist was used as a guide for reporting this study protocol.

Prior to participation, interested participants will have access to the written informed consent online form, which will include details of the trial, explanation about potential risks and benefits and contact information of the research members. Participants will know that the intervention is completely optional and can be discontinued at any time. Written informed consent will be obtained online by pressing the consent button when the participant agrees to participate in the trial, before any intervention and assessments are provided.

### Confidentiality

Data security/confidentiality will be guaranteed according to Spanish Organic Law 3/2018 of December 5 on the Protection of Personal Data and Guarantee of Digital Rights and all relevant EU and Spanish privacy laws will be observed and respected.

Access to the web platform will be granted via a unique username-password combination. Data collected via the website will be stored on secure servers at University of Valencia (UVEG) with personal data and user-generated data stored in separate databases on different servers. The consent form will be explained and required from all participants at the eligibility assessment.

Data will be kept for a maximum of 5 years after the end of the project and participants will have the right to access, rectify personal information, withdraw consent and request deletion of their personal data.

### Access to data

Prior to the publication of the results, only data managers and principal investigators will have access to the database, will address any problem related to the data and finalize a dataset for statistical analysis.

After publication, data will be accessible on a digital platform following the procedure stated by fair guideline principle.

### Ancillary and post-trial care

Participants will be able to contact the researchers during the trial period or until 3 months after the end of participation. Although serious adverse events are not expected, if any participant develops any adverse event, they will be responded to promptly and appropriately even after study completion.

### Dissemination policy

Results from this trial will be published and disseminated in a peer-reviewed journal and public presentations at scientific and clinical conferences. Moreover, participation at important national and international academic conventions will be delivered and results will be shared to the general population and interested stakeholders via social media to further promote dissemination of the results.

## Results

Enrollment started in April 2021 and will be finished in April 2021. Data analysis will start in January 2022.

## Discussion

The objective of this paper is to describe the study protocol of a RCT designed to explore the efficacy of the iABCT on a population with chronic medical illness.

Recent evidence has highlighted the training of compassion and self-compassion as an effective approach to chronic medical illness [29, 30]. Moreover, online adaptations of these treatments suppose a highly-accessible and sustainable mode of delivery which improves psychological outcomes among people living with these medical conditions [38, 41].

Although promising studies have been aimed at exploring the adaptation of CBI to an online format on populations with chronic medical illnesses [40, 41], research in this context is still scarce and deeper exploration is needed. To our knowledge, this is the first attempt to explore the efficacy of the iABCT on improving the quality of life in a population with chronic medical illnesses.

The approach of the iABCT is based on the attachment styles theory [31]. The aim of this intervention is to build a secure attachment style through the training of compassion and self-compassion, which has been considered as a key therapeutic factor [31, 80]. It is expected that those improvements will help individuals with chronic conditions to approach their illness and related difficulties with a kind and compassionate response. This, in turn, would promote self-care behaviors and improve their illness management, thus leading to a higher quality of life and well-being.

Furthermore, since different aspects of the intervention implementation and mechanisms of change will be investigated, this study has potential to shed light on the relationships between the different constructs assessed together with compassion and self-compassion outcomes (e.g., self-criticism, attachment styles) and to extend our current understanding of barriers and facilitators of CBIs delivered online in the context of chronic medical illness.

This trial has some limitations that require consideration. First, since the control group in the current study is a waitlist control rather than active control, relative utility of the iABCT will not be explored. Future studies could benefit from including an active control to explore relative utility of the modality (e.g. comparing Internet version of the ABCT with the original treatment) or the treatment approach (e.g. comparing iABCT with iCBT). Secondly, since stratification will not be balanced, some comparative analysis will not be possible to explore if sample size of each group is not sufficient and equal to each group (e.g. comparisons regarding specific illness interference across different types of chronic medical conditions).

Despite these limitations, findings from this study will add valuable data to the incipient research field on the potential of self-applied CBIs via the internet in the context of chronic medical illnesses [40, 41].
